##### Reminder procedures

In case of no response from healthcare professionals, we will ask practice nurses to remind non responding persons in their general practice. In case of no response from patients we will send letters as reminders.

### Outcomes & measures

#### **
*Primary outcomes for health professionals*
**

Baseline and 6-month follow-up measures will be conducted for health care professionals, patients, and their alters.

### Health care professionals and their alters

Main outcomes for health professionals will consist of 1) the description of social networks and 2) the hypothesized effects of several social network characteristics, controlled for possibly confounding variables, on professional performance of practice nurses and patients’ health outcomes. Additionally, exploration of effects on social network characteristics on changes in professional performance after completion of the RCT are of main interests.

#### 

**Professional performance** Professional performance reflects application of recommendations for personalized counseling and education of CVRM patients by practice nurses. Professional performance is represented with a dichotomous score, reflecting adequate or inadequate performance. We will consider personalized lifestyle advice as provided by practice nurses to be adequate when at least one of the following conditions is met:

1. There is a record in the patients’ medical file or other healthcare provider-based records that the patient has received advice on at least one lifestyle item as specified in prevailing guidelines of CVRM; diet, smoking or physical exercise, and which has been relevant for the individual patient in the previous six months. At least one target, made up maximally 15 months ago, for improving an aspect of lifestyle should be recorded. Also, practice nurses are required to make a register note when a patient has an adequate lifestyle.

2. There is a notation in the patients’ medical file that the patient has none, mild or major depressive symptoms and that the patient has been referred to E-health, a physical exercise group, or depression treatment respectively.

#### **
*Other measurements on health care professionals will include*
**

##### 

**Descriptive variables** Descriptive measures will include size of practice (number of staff and patients), profession, and involvement in other organizations or projects and will be measured using the Epa Cardio abstraction tool for medical audit instrument [32].

##### 

**Information items for constructing social networks** For constructing social networks we will use a specifically developed and personalized roster questionnaire (see Additional file 2: Appendix 2a for the network questionnaire for health professionals from general practices participating in the RCT and Additional file 2: Appendix 2b for the network questionnaire of alters of health professionals). On this network roster, health professionals will be asked to indicate their social contacts for CVRM information sharing and receiving on two subjects:

1) medical policy for CVRM in general and on 2) CVRM for specific patients. In this network roster, names are listed of all persons involved in patient care within a general practice so that respondents can tick names of persons with whom they share information. Also, space is provided for names of persons outside the general practice, respondents are asked to fill out these names themselves.

##### 

**Frequency of contact** For measuring frequency of contact for information sharing, health professionals are asked to indicate whether they have been in contact on a 1) daily/weekly or 2) monthly/yearly basis with each person they share information with.

##### 

**CVRM-coordinators** For the identification of the presence of CVRM-coordinators within general practices we will ask health professionals to list the name(s) of the person(s) responsible for coordination of CVRM within the particular general practice.

##### 

**Opinion leaders** For the identification of opinion leaders we will ask health professionals to write down the name and occupation of the person they consider to have ‘a significant influence on their current practice in CVRM’. Health professionals will be instructed that this person can be anyone from inside or outside the general practice, and that the influence this person has had can be either current or from the past.

##### 

**Priority for preventive treatment and CVRM targets** For determining whether social network characteristics are related to certain attitudes on clinical processes for CVRM, and whether these attitudes are more or less present in certain social networks, we will measure priority for preventive treatment and achievement of CVRM targets by presenting five statements containing general recommendations and targets for CVRM (e.g. ‘for patients with a high risk for CVD, strive for a systolic blood pressure < 140 mmHg’). These items were selected from current guidelines and previous research indicated [32] that primary care for these items can be enhanced. Health professionals are asked to indicate on a 5-point Likert scale (1: totally unimportant – 5: highly important) how important they consider ‘a change in direction of the presented target’ as indicator for priority for preventive treatment and ‘achievement of the presented target’ as indicator for priority for CVRM targets.

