## Methods

### Study design

This observational research is part of the ‘Tailored Implementation for Chronic Diseases’ (TICD) project. The TICD-project has the overall aim to develop and test methods of tailoring implementation interventions to determinants of practice in chronic illness care in five different chronic conditions in five different countries in Europe [29].

This study will be performed parallel to a two-arm RCT as developed by the Dutch team (trial registration: NTR4069). This approach is chosen as it will allow for both the investigation of network characteristics for quality of current CVRM care by health professionals and self-management of patients and for associations of network characteristics with changes in quality of CVRM care and self-management after completion of the RCT intervention program. The RCT aims at enhancing primary care for CVRM by improving professional performance of practice nurses [30]. Practice nurses conduct care for patients with chronic conditions. They provide patients with education and guidance about their disease, medication-use, and changes in lifestyle and independently perform consultation hours and regular checkups.

For this RCT, comparing an intervention vs a control (postponed intervention) group, a tailored intervention package has been developed which offers practice nurses several options for enhancing their knowledge on CVRM and counseling skills. Additionally, the package provides recommendations for referral of patients. This package consists of training and feedback on motivational interviewing technique and an e-learning program on CVRM. Also, practice nurses will be advised to pay particular attention to the presence of depressive symptoms and plan action according to these as patients with CVD have a higher risk for experiencing depressive symptoms [27] with concomitant impairments in altering self-management [20]. More specifically, practice nurses are recommended to refer patients without depressive symptoms to e-health learning modules, patients with mild depressive symptoms to a physical exercise group, and patients with severe depressive symptoms to psychological help as appropriate in their practice [30]. Data on professional performance of practice nurses, patients’ self-management and treatment outcomes will be measured at baseline and follow-up at six months after the start of this intervention [30].

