In the analyses of self-management and health outcomes in patients, several multivariate logistic regression models will be estimated. For self-management, separate models will be estimated on physical activity, diet, and smoking. For health outcomes, separate models will be estimated on SBP, cholesterol, and risk score. Models will include four network characteristics as predictors: number of alters with favorable health behaviors, who are also connected among each other, number of alters with depressive symptoms, and number of alters who can provide CVRM-related information. The regression models will be controlled for trial arm (intervention vs control group), patient group (high risk or established CVD), and several personal characteristics: age, sex, ethnicity, marital status, SES, patient activation, therapy adherence, and depressive symptoms.

Two approaches will be used to investigate effects of social network characteristics on change in professional performance of practice nurses and self-management and health outcomes of patients after the intervention period at six month follow-up. First, follow-up outcomes measures will be treated as dependent variables. We will estimate similar models as described above and include baseline measures of outcomes of interest as predictors. Second, we will consider change as the difference between the baseline- and follow-up measures of the diverse outcomes of interest. Ordinal logistic regression models will be estimated, with change represented in three categories; a shift from inadequate to adequate outcomes, no change, and shift from adequate to inadequate outcomes.

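### At six-month follow-up, professional performance can be scored adequate from entries made before baseline, so lapses in patients already adequate are hidden as no change

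*Protocol article*

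**What the plan says.** The definition is in the protocol article, under Health care professionals and their alters, Professional performance. The score is a dichotomy, and care counts as "adequate when at least one of the following conditions is met".

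- **Condition 1** needs a record of advice on at least one lifestyle item, "which has been relevant for the individual patient in the previous six months". It also needs a target: "At least one target, made up maximally 15 months ago, for improving an aspect of lifestyle should be recorded". Nurses must also note when a patient's lifestyle is already adequate; no date limit is attached to that note.
- **Condition 2** has two parts. One is an entry on depression: "There is a notation in the patients’ medical file that the patient has none, mild or major depressive symptoms". The other is a recorded referral of the kind that matches the symptom level. No look-back period is stated for either.

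On timing, Study design says that performance data "will be measured at baseline and follow-up at six months after the start of this intervention", and Outcomes & measures repeats it: "Baseline and 6-month follow-up measures will be conducted for health care professionals, patients, and their alters". Nothing in the article requires an entry counted at follow-up to have been made after baseline.

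Statistical analyses then studies change in two ways. The first models the follow-up outcome with the baseline outcome as a predictor. The second is an ordinal model with three categories: "a shift from inadequate to adequate outcomes, no change, and shift from adequate to inadequate outcomes". Aim 3 under Research aims is to explore the influence of network characteristics on such change, and the outcome section calls this a main interest.

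**The concern.** A score taken twice, six months apart, can show what happened in between only if the second score depends on that period. Here one element looks back 15 months, one whole route to adequacy has no limit, and the routes are joined by 'or'. Some patients can therefore be scored adequate at follow-up on the same entries that made them adequate at baseline.

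This bears on aim 3. If practices with different networks differ in how well they keep up care for patients already adequate, that difference is partly or wholly invisible. A null result would be hard to read, because absence of a network effect and a follow-up score partly copied from baseline would look alike.

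**Working it through.** The article gives no figure of its own on this point to reproduce. The only sample size it derives, 338 patients, concerns response rates and is not affected.

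**Inputs from the article.** Interval between measurements: 6 months. Look-back for the target: 15 months. Look-back for condition 2: none stated. Combination rule: either condition. The frequencies of targets, advice, notations and referrals are not given. I take the baseline measurement to coincide with the start of the intervention.

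**Step 1: overlap of the target window.** 15 − 6 = 9 months of the follow-up window lie before baseline; 9/15 = 60%. This is a share of calendar time, not of patients.

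**Step 2: what the overlap does.** Take two patients with a target before baseline and none after it, alike in all else. A target set 8 months before baseline is 8 + 6 = 14 months old at follow-up and still counts. One set 10 months before is 10 + 6 = 16 months old and does not. Their change category can differ because of a date before the study, not because of care during it.

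**Step 3: which elements can carry over.**

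| Element | Six-month clause dates the advice | Clause dates only the item's relevance |
|---|---|---|
| Condition 1, advice | No; advice after baseline is needed | Yes, while the item stays relevant |
| Condition 1, target | Yes, if set within 9 months before baseline | Same |
| Condition 2, notation and referral | Yes, always | Yes, always |

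An old target alone never makes a patient adequate, because the advice element must also be met. Through condition 2 carry-over is complete: an entry counted at baseline counts again.

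**Step 4: illustration for the target element only.** Assume targets are recorded at a constant rate, and let q be the share of patients with at least one target in 15 months. The chance of none in t months is (1 − q)^(t/15).

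- Met at follow-up only through a pre-baseline target: [1 − (1 − q)^(9/15)] × (1 − q)^(6/15).
- Share of those meeting it at follow-up: that figure divided by q.
- Share of those meeting it at baseline who still meet it if no target is set afterwards: [1 − (1 − q)^(9/15)] / q.

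| q (assumed) | Met only by pre-baseline target, of all patients | Of those meeting it at follow-up | Still met with no new target |
|---|---|---|---|
| 30% | 16.7% | 55.7% | 64.2% |
| 50% | 25.8% | 51.6% | 68.0% |
| 70% | 31.8% | 45.4% | 73.5% |

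If the clause requires fresh advice, multiply the second column by the probability of such advice, taken as independent of the target's date. At 50% it becomes 8.4%, 12.9% and 15.9%; at 0% it is zero. These figures show how wide the plausible range is. They do not estimate misclassification in this study.

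**Step 5: direction of the effect.** A patient adequate at baseline can only stay adequate or lapse. Carry-over moves lapses into 'no change', and it gives the same category to a patient with new activity and one with none. A patient inadequate at baseline has no complete qualifying record to carry over. If an old target is completed by new advice, that is real new activity and is rightly scored as improvement.

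**The case against.** **The case for leaving it alone.** Performance is an outcome of the parent RCT, whose protocol is cited but not shown; abstraction rules, including a limit for condition 2, may be there. Applying a 15-month limit already means reading entry dates. The condition 2 referrals match the recommendations in the RCT's intervention package, so few may exist before baseline. A strict six-month window would score as inadequate a patient whose target was set eight months earlier and is still being pursued, and would depart from the RCT definition. Aim 3 is exploratory.

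Most of this stands as a limit on size and severity. It does not remove the point: the definition as printed is explicit, is applied twice, and allows pre-baseline entries to count at follow-up.

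**Stronger readings that the article does not support.**

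- A reader might infer that an old target by itself keeps a patient adequate. It does not, and the six-month clause can be read as requiring recent advice.
- A reader might infer that improvement is diluted. Patients inadequate at baseline have nothing complete to carry over, and patients adequate at baseline cannot improve on a dichotomy under any window.
- A reader might try to size the loss by shrinking a between-practice difference at follow-up by an assumed carry-over share c. That models neither change analysis, since baseline is absent, and it requires equal c in all practices. If new activity were 40% v 25% and c were also 40% v 25%, the difference would be (1 − 0.60 × 0.60) − (1 − 0.75 × 0.75) = 64.0% − 43.75% = 20.25 points, larger than the assumed 15. Neither size nor direction follows from such a formula.

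**Conclusion.** The point holds in a limited form. As written, 60% of the target window at follow-up is pre-baseline time, and a patient adequate at baseline through condition 2 cannot be scored as lapsed. Condition 1 carries over its target element, and its advice element only under one reading of an ambiguous clause. The consequence is mainly one-directional: lapses, and differences in new activity, among patients adequate at baseline are recorded as no change, which weakens both change analyses for aim 3.

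How many patients this touches is unknown, and the shares in the illustration rest on assumed frequencies and a constant recording rate. The cross-sectional analysis (aim 2), the patient self-management and health outcomes, the response-rate comparison and the sample size are unaffected. Severity is moderate.

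**What to change.** 1. Have the abstractor record the date of each advice, target, adequate-lifestyle note, depression notation and referral.
2. State whether the six-month clause dates the advice or only the relevance of the item, and state what period condition 2 covers for scoring purposes.
3. For the aim 3 change analyses, prespecify a version, at least as a sensitivity analysis, that counts only entries dated in the six months before each measurement, so that the follow-up score rests on entries made after baseline. Apply it to both conditions.
4. Keep the existing definition for aim 2 and for agreement with the RCT.

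The cost is date fields on the abstraction form and one derived variable. Fewer patients will be scored adequate in the added version, and two versions must be reported. This should be settled before abstraction: if dates are not captured then, up to 900 files would have to be reopened.

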### Primary outcomes for patients

#### **
*Patients and their alters*
**

Main outcomes for patients will consist of 1) description of social networks, 2) response rates after different invitations for participation in the network study, and 3) the hypothesized effects of several social network characteristics, controlled for possibly confounding variables, on self-management and health outcomes. Additionally, exploration of effects of social network characteristics on changes in self-management and health outcomes after completion of the RCT are of main interest.

##### 

**Response rates** One of the main outcomes for patients are response rates of including patients by inviting them with either 1) an invitation with one option to participate in the social network study or 2) an invitation to participate in the research with two options so that patients can indicate their preference for participating by a telephone interview or a paper-based questionnaire.

##### 

**Self-management** Self-management will be measured using a composite questionnaire on physical activity; *Rapid Assessment of Physical Activity (RAPA), 9 items*[33], diet; *reduced Rapid Eating and Activity Assessment (REAP-s), 12 items*[34], and smoking; *(MID-SIZED Model), 8 items*[35].

Scores on the RAPA ≥ 5 indicate sufficient physical activity. The REAP-s asks how often persons engage in particular diet patterns in a regular week (e.g. high sugar/calorie sweets and beverages intake), using four response categories (‘often/usually’, ‘sometimes’, ‘rarely’, and (for items where appropriate) ‘not applicable’). Patients who score ≤ 5 items on the REAP-s as ‘often/usually’ will be considered to have a healthy diet. Current smoking status is indicated by a dichotomous score (yes/no).

##### 

**Health outcomes** Health outcomes will consist of SBP, cholesterol, and risk score. Thresholds for desired treatment values for SBP and cholesterol may differ for patients at risk, with established CVD, patients of certain ages, and according to individual targets set in agreement with treating health professionals and will be analyzed accordingly. Risk scores, only applicable to patients without established CVD, will be calculated using prevailing risk estimation tables [36]. The following parameters will be used in the calculation: age, gender, smoking status, systolic blood pressure (SBP) and total cholesterol/HDL-cholesterol ratio. The Epa Cardio abstraction tool [31] for medical audit will be used for abstracting these health outcomes.

#### **
*Other measures on patients will include*
**

##### 

**Descriptive variables** Descriptive measures will include age, sex, ethnicity, marital status, educational level, and social economic status (SES). For data collection we will use a questionnaire containing items from the Epa cardio abstraction tool [32].

##### 

**Information items for constructing social networks** For constructing and measuring social networks, patients are asked to indicate on a network roster from which persons they have received information on 1) medical treatment, 2) handling their condition or disease, and 3) practical help. We will provide a specifically developed and personalized roster questionnaire with names and disciplines of health professionals from their general practices (see Additional file 3: Appendix 3a). Patients are offered the possibility to add names of other persons (healthcare professionals/people in personal circle) they have received information from.

Alters are asked to indicate on a network roster to which persons they have provided information on 1) medical treatment, 2) handling their condition or disease, and 3) practical help using a specifically developed and personalized roster questionnaire (see Additional file 3: Appendix 3b).

##### 

**Frequency of contact** For measuring frequency of contact, patients will be asked to indicate how often they have received information from persons who have provided information in the last year. Similarly, alters will be asked how often they have provided information.

##### 

**Central care providers** A central care provider represents the health professional patients will contact first when they have questions regarding a specific condition or disease and who coordinates care when multiple health professionals are involved in treatment.

For identification of central care providers we will ask patients to write down the name of the person they consider to be their central care provider for CVRM, specified as ‘the first person they would approach in case of uncertainties or troubles regarding their condition or disease’.

##### 

**Opinion leaders** For identification of opinion leaders patients will be asked to write down the name of the person they consider ‘to be most important for dealing with disease or lifestyle’. Patients will be instructed that this person doesn’t need to be ‘most important’ for a specific reason and that this person doesn’t need to be part of the patient’s personal environment.

##### 

**Number of alters with appropriate self-management** For assessing what number of alters in patients’ networks have adequate self-management we will ask patients to indicate whether he/she believes that their indicated alters smoke, have a healthy diet, and engage in sufficient physical activity. In addition, we will ask alters of patients to complete questionnaires on their lifestyle habits (smoking; *(MID-SIZED Model, 8 items*[35]), diet; *reduced Rapid Eating and Activity Assessment (REAP-s), 12 items*[34], and physical activity; *Rapid Assessment of Physical Activity (RAPA), 9 items*[33].

##### 

**Connectedness of alters** For assessing whether alters of patients are also connected to each other, we will use information from the network rosters completed by all alters of a given patient.

##### 

**Number of alters with depressive symptoms** For assessing whether alters with depressive symptoms are present in patients’ networks we will ask alters of patients to complete the Patient Health Questionnaire (PHQ-9) [37], which is a short questionnaire for depression.

##### 

**Number of alters providing access to CVRM information** For assessing how many persons who can provide access to CVRM information are available in patients’ social networks we will ask patients to indicate how many of the persons from whom they receive CVRM related information have a medical occupation or have been educated for this.

##### 

**Personal characteristics** For assessment of personal characteristics of patients we will measure patient activation (*Patient Activation Measure, PAM*[38]), therapy adherence (*Medication Adherence Measure*[39]), quality of life (*EQ-5D*[40]), and depressive symptoms (*Patient Health Questionnaire, PHQ-9*[37]). Alters of patients will complete the PHQ-9. Higher total scores on these measures will indicate higher patient activation, therapy adherence, quality of life, and depressive symptoms respectively.

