### Sample size calculation

The RCT study, in which the present research is embedded, is powered to detect a 15% difference in provided personalized lifestyle advice by including 900 patients clustered within 30 practices [30]. For the present research, we calculated the sample size for detecting a 15% difference in response rate of patients who are approached by 1) an invitation for participation in this study with a telephone interview) and 2) the choice for participating by a telephone interview or a paper-based test. Assuming alpha is 0.05, power of 0.80, a response rate of 50% in the first group and 65% in the second group, we estimated that we need to include 338 patients.

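### Diet and physical activity are scored on graded instruments but analysed only as adequate or inadequate, in level and in change; this discards power that a wording change would recover.

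*Protocol article*

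**What the plan says.** Under *Primary outcomes for patients*, self-management consists of physical activity, diet and smoking. The diet instrument is the "reduced Rapid Eating and Activity Assessment (REAP-s), 12 items", so the number of items answered 'often/usually' can run from 0 to 12. The rule is that "Patients who score ≤ 5 items on the REAP-s as ‘often/usually’ will be considered to have a healthy diet". For activity, "Scores on the RAPA ≥ 5 indicate sufficient physical activity". Smoking is recorded as yes or no.

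Under *Statistical analyses*, patient outcomes are analysed with logistic regression: "For self-management, separate models will be estimated on physical activity, diet, and smoking". Six-month change is approached in two ways. The first refits similar models to the follow-up outcome with the baseline outcome as a predictor. The second is an ordinal logistic model with "change represented in three categories; a shift from inadequate to adequate outcomes, no change, and shift from adequate to inadequate outcomes". No model takes the REAP-s count or the RAPA score itself as its outcome.

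**The concern.** The REAP-s rule cuts twice. Each item becomes 'often/usually' or not, and the resulting count becomes 5 or fewer against 6 or more. The three-category change analysis then sees only crossings of that line. A fall from 12 items to 6 is no change, while a fall from 6 to 5 is an improvement. The article gives no reason why either cut has to be the scale of analysis.

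Self-management is a main patient outcome and comes first in the patient hypothesis; change in it is part of the third research aim. Information is not plentiful. Patients join the network study by separate invitation. At the response rates assumed for the sample size (50% and 65%), 450 to 585 of 900 patients would supply detailed network data (0.50 × 900 and 0.65 × 900), before any loss of alter questionnaires. Each patient model carries four network predictors plus trial arm, patient group and eight personal characteristics. Discarding graded information that has already been collected makes a real association easier to miss.

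**Working it through.** **The plan's own figure.** The only sample size calculation for the network study concerns response rates: "Assuming alpha is 0.05, power of 0.80, a response rate of 50% in the first group and 65% in the second group", from which "we estimated that we need to include 338 patients". The pooled two-proportion formula at two-sided 5% gives 170 per group, 340 in total. The arcsine formula gives 169.1 per group, 338.2 in total. The figure reproduces, but it says nothing about self-management. The other figure in that section, "by including 900 patients clustered within 30 practices", concerns the RCT endpoint. No effect size, standard deviation, healthy share or power is given for diet or activity, so these are assumptions below.

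**Level: formula.** For a normal underlying score cut so that a proportion p is healthy, the information kept relative to the full scale is

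E = φ(z_p)² / [p(1 − p)].

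If the graded analysis has 80% power at two-sided 5%, the cut analysis has power

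Φ((1.96 + 0.842)·√E − 1.96).

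Example, p = 0.8: E = 0.490, √E = 0.70, 2.802 × 0.70 − 1.96 ≈ 0.00, so power is 50%.

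| Assumed healthy share | E | Power with the cut | Loss (points) | Patients needed to recover (1/E) |
|---|---|---|---|---|
| 50% | 0.637 | 61% | 19 | 1.57 × |
| 70% | 0.576 | 57% | 23 | 1.74 × |
| 80% | 0.490 | 50% | 30 | 2.04 × |
| 90% | 0.342 | 37% | 43 | 2.92 × |

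The loss depends on where graded power lies. Over healthy shares of 50% to 90% it is 9 to 17 points at graded power 30%, and 6 to 28 points at 99%.

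**Level: simulated 0–12 count, cut at 5 or fewer.** With n = 338, 450 or 900, standardised associations of 0.10 or 0.15 and 58% to 90% healthy, the loss ranged from 5 to 44 points, mostly 11 to 33. The losses of 5 to 8 points arose only where n = 900 and graded power was already about 99%. Where graded power was 75% to 80% (n = 338, association 0.15), the losses were 18 to 21 points at 58–60% healthy, 26 to 28 at 72–77%, and 32 to 44 at 84–90%, close to the formula. A second simulation, using a logit shift of the count, gave about 80% against 64–65% at 50% healthy and 79–80% against 39–42% at 92%.

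**Change.** Normal scores were simulated with n = 450 or 900, association 0.08 or 0.10, baseline correlation 0.5 or 0.7 and 50%, 70% or 85% healthy. Against the follow-up score adjusted for the baseline score, logistic regression on follow-up status adjusted for baseline status lost 17 to 52 points. The three-category shift lost 31 to 60, with a linear trend test standing in for the ordinal model. For instance, with n = 900, 70% healthy, correlation 0.5 and association 0.08, the powers were 80%, 49% and 35%.

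**Limits.** All simulations ignore clustering by practice and the covariates. RAPA was not simulated on its own scale, and the article does not give its range. The formula compares the cut with a continuous scale, so for a coarse score it may overstate the loss. The article does not say whether the baseline predictor at follow-up is the status or the score; the simulation used the status.

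**The case against.** The cuts match the question asked. The patient hypothesis is about being more likely to have favourable self-management. The main exposure is also a status, the number of alters with adequate behaviour, and smoking is binary in any case. One adequate/inadequate metric throughout is coherent and easy to read. If network influence acts mainly at the line between inadequate and adequate behaviour, a cut would lose less and might even do better; no such scenario was run, since the calculations assume a shift along the whole scale. The aims and hypotheses are described as exploratory. The 12-to-6 example is extreme, and nothing shows how common such moves are. Analysing the count still leaves the item-level cut in place, and some items allow a 'not applicable' answer.

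Much of this stands as qualification. It does not remove the point. A proportional-odds model on the score estimates the odds of a more favourable level, which remains a reading of the hypothesis, and the cut-based results stay available. Exploratory aims also suffer from missed associations.

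**Conclusion.** The point holds as one of efficiency, for diet and physical activity. The cuts, the model family and the change categories are all stated choices, so this is not detail left to an analysis plan. The size is conditional: a loss of 19 to 43 points if the graded analysis had 80% power, 50% to 90% of patients were healthy and the association shifted the whole scale. The loss is smaller when graded power is very low or close to 100%. It is larger for the three-category change analysis under the assumptions simulated.

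A reader might infer three stronger things that the article does not support:
- A fixed number of power points is lost on the patient hypothesis. The article supplies none of the inputs needed to say so.
- The plan fails a power it promised. It states none for self-management.
- All of self-management is affected. Smoking is not.

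This is a worthwhile and cheap improvement rather than an error that invalidates the analysis.

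**What to change.** In *Statistical analyses*:
- Make the REAP-s 'often/usually' count and the RAPA score the main diet and activity outcomes, each in a proportional-odds model with the same network predictors and covariates. State how 'not applicable' answers enter the count.
- For change, model the follow-up score adjusted for the baseline score of the same instrument.
- Keep the healthy-diet and sufficient-activity cuts and the shift categories as supportive results. Leave smoking binary.

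This needs no new data, patients or software: R and ordinal logistic models are already planned. The cost is one of interpretation. The main coefficient becomes the odds of a more favourable score rather than the odds of passing the cut, and the retained cut-based results still supply the latter.
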